### Secondary outcome measures

The secondary outcome measures will test the feasibility of telephone and video follow-up and specifically the benefit to trial retention of remote methods (i.e. maintenance of a patient with trial follow-up to the end of the study, in this case 30 days after surgery).
Retention benefit: ratio of the proportion of recruited patients returning a telephone WHQ to the proportion of recruited patients completing in-person follow-upTelephone contact rate: proportion of patients successfully contacted by the telephoneReturn rate: the proportion of telephone WHQ returned, and reasons not completedData completion rate: proportion of missing data within each formVideo contact rate: proportion of patients successfully contacted for a live video wound assessment

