### Eligibility criteria

Consecutive adult patients (greater than 18 years) recruited to the FALCON or ChEETAh study that are likely to return for routine in-person follow-up at around 30 days postoperatively are eligible. Consent for an additional telephone follow-up call within the TALON-2 study will be taken at the same time as trial consent, using a targeted Informed Consent Form and Patient Information Sheet. Community representatives will co-produce these resources to ensure culturally appropriate language and delivery.

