### Sample size

As TALON-2 is a validation study for a diagnostic criterion, no formal sample size calculation is required. A range of sample sizes and their impact on the 95% confidence interval (CI) around estimates of sensitivity 0.92 and specificity 0.95 based on a prevalence of 0.21 using the binomial exact formula are presented in Table 1. Sample sizes are adjusted to allow for 15% loss to follow-up from the host trials, and 15% of patients who do not achieve both telephone WHQ completion and 30-day in-person follow-up within TALON-2. Sampling from Hub and Spoke centres across several LMICs will give a representative sample of urban and rural settings.

**Table 1 Tab1:** TALON-2 study sample size estimates

Patients recruited to host trial	Patients retained for follow-up	Paired WHQ and in-person follow-up	Patients with SSI^a^	Patients without SSI^b^	Precision around test accuracy measures	
					Sensitivity (95% C.I.)	Specificity (95% C.I.)
714	607	516	108	408	0.92 (0.85–0.96)	0.95 (0.93–0.97)
571	485	412	87	325	0.92 (0.84–0.97)	0.95 (0.92–0.97)
428	364	309	65	244	0.92 (0.83–0.97)	0.95 (0.92–0.97)
285	242	206	43	163	0.92 (0.81–0.99)	0.95 (0.91–0.98)

^a^0.21 * number paired WHQ and in-person follow-up

^b^0.79 * number paired WHQ and in-person follow-up

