## Discussion

TALON is a large international collaborative cohort study which will evaluate a telephone follow-up pathway for surgical site assessment following abdominal surgery across seven low- and middle-income countries. This will allow researchers to better understand both the feasibility and validity of remote follow-up for SSI across diverse settings. Remote follow-up methods are an attractive target for improving trial retention; this study is designed to compare the within-participant attrition rates between in-person and telephone follow-up in-depth. Through adaptation and translation of an existing patient-reported outcome measure, TALON will provide a package of tools for surgical researchers across cultural and language contexts. Finally, TALON will adopt a novel and efficient study within a trial (SWAT) design, which provides an attractive future model for methodological research in global surgery.

Methods of post-discharge follow-up which do not require face-to-face review have grown rapidly in interest over the past 5 years [48, 49]. Exponential advances in global access to telecommunications and mobile devices have been bolstered by a global momentum towards telemedical delivery of postoperative care during the SARS-COV-2 pandemic [50–52]. The World Bank estimates that over 80% of the population of sub-Saharan Africa now have access to a mobile telephone, and this continues to increase year-on-year [18]. Remote follow-up has several advantages to patients in LMICs and research studies. Firstly, patients can avoid significant additional costs of transport and time out of work associated with return to hospital [53]. Secondly, telemedicine may reach patients who are unable to return to the hospital for reasons of costs, access, or logistics, improving trial retention [6, 24, 54, 55]. Thirdly, it can protect scarce time for busy LMIC clinicians and improve trial efficiency [56]. However, rapid implementation of unvalidated digital follow-up methods into randomised trials (or indeed clinical practice) may risk harm to patients through missed infection, overtreatment, and/or introducing research bias [24]. Existing evidence is available only from small, low-quality studies at high risk of bias and/or without adopting a diagnostic accuracy frame of evaluation [54, 57–60]. This large, pragmatic study aims to fill this knowledge gap by exploring the feasibility and accuracy of a novel remote follow-up pathway.

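### The TALON-2 retention-benefit ratio compares telephone as a replacement for in-person follow-up; it does not show how many in-person non-attenders the telephone recovers

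*Protocol article*

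**What the plan says.** The TALON-2 section on secondary outcome measures says these outcomes test "specifically the benefit to trial retention of remote methods (i.e. maintenance of a patient with trial follow-up to the end of the study", here day 30. Its first listed outcome, retention benefit, is the "ratio of the proportion of recruited patients returning a telephone WHQ to the proportion of recruited patients completing in-person" follow-up. The other listed outcomes are the telephone contact rate, the questionnaire return rate with reasons for non-completion, the data completion rate and the video contact rate.

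The Discussion gives the mechanism by which retention should improve: "telemedicine may reach patients who are unable to return to the hospital for reasons of costs, access, or logistics, improving trial retention". It also states that "this study is designed to compare the within-participant attrition rates between in-person and telephone follow-up in-depth".

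The Sample size section supplies the only planning losses: "Sample sizes are adjusted to allow for 15% loss to follow-up from the host trials", and then "15% of patients who do not achieve both telephone WHQ completion and 30-day in-person follow-up within TALON-2". The article gives no expected value or threshold for the retention-benefit ratio.

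**The concern.** Both assessments are attempted in every TALON-2 patient, so each recruited patient falls into one of four cells: both completed, in-person only, telephone only, or neither. The gain described in the Discussion lies in the telephone-only cell. The ratio uses only the two overall proportions, so a patient seen in person but missed by telephone offsets a patient reached only by telephone. If telephone is added to in-person visits, the first patient is not lost to the trial and the second is the gain.

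None of the other listed outcomes is defined among in-person non-attenders or as follow-up by either route. The Statistical analysis section does compare patients with and without in-person assessment, but to look for verification bias. As defined in the article, the outcome labelled as the retention benefit could therefore be reported without saying how many patients were recovered.

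**Working it through.** **Inputs.** From Sample size and Table 1: a 15% host-trial loss, then a further 15% without a complete pair. The first five entries of the top row are "714 607 516 108 408": recruited, retained, paired, with SSI, without SSI. The telephone return rate among in-person non-attenders is not given, so it is varied from 0 to 1.

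**Reproducing Table 1.** 714 × 0.85 = 606.9, printed as 607. 714 × 0.85 × 0.85 = 515.9, printed as 516. The attrition chain reproduces.

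**Formulas.** Let π be the proportion completing in-person follow-up, q the telephone return among those attenders, and r the telephone return among non-attenders.

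- Protocol ratio = [πq + (1 − π)r] / π = q + r(1 − π)/π
- Follow-up by either route = π + (1 − π)r

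The ratio mixes q and r. Follow-up by either route depends on r only, for a given π.

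**Same ratio, different recovery (π = 0.85).**

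- q = 1, r = 0: ratio = 0.85/0.85 = 1.00; either route = 85%.
- q = 0.85, r = 0.85: ratio = (0.7225 + 0.1275)/0.85 = 1.00; either route = 0.85 + 0.15 × 0.85 = 97.75%.

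**Reading A of Table 1 (assumption: retained means in-person completed, and the missing half of each incomplete pair is the telephone questionnaire).** Then π = 0.85 and q = 0.85, and the ratio is 0.85 + 0.176r.

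| Non-attenders recovered (r) | Protocol ratio | Either route |
|---|---|---|
| 0 | 0.85 | 85% |
| 0.50 | 0.7975/0.85 = 0.94 | 92.5% |
| 0.85 | 1.00 | 97.75% |
| 1 | 0.8725/0.85 = 1.03 | 100% |

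**Reading B (assumption: every incomplete pair lacks only the in-person visit).** In-person = 0.7225 and telephone is at least 0.85, so the ratio is at least 0.85/0.7225 = 1.18. Non-attenders are 27.75% of recruits, of whom at least 12.75 points are reached by telephone, so r is at least 0.1275/0.2775 = 0.46.

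**Reading C (assumption: incomplete pairs split evenly between the two).** In-person = 0.7225 + 0.1275/2 = 0.786 and telephone is at least the same, so the ratio is at least 1.00.

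Reading A with r = 0.50 gives 0.94, and Reading B with r = 0.46 gives 1.18. Recovery is similar, but the ratios fall on opposite sides of 1.

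**Sensitivity to q (π = 0.85).** The ratio equals 1 at r = 0.85(1 − q)/0.15. That is 0.28 for q = 0.95, 0.57 for q = 0.90, 0.85 for q = 0.85 and 1.13 (unattainable) for q = 0.80.

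**Sensitivity to π (q = 0.85, r = 0.75).** The ratio is 1.17, 1.04, 0.98, 0.93 and 0.89 for π = 0.70, 0.80, 0.85, 0.90 and 0.95. Patients "likely to return for routine in-person follow-up at around 30 days postoperatively are eligible" for TALON-2, and centres are chosen on the same ground. Both tend to raise π and so shrink the weight (1 − π)/π given to recovered patients.

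**The case against.** The strongest reply is that the ratio is a valid measure for a question the article does ask. The Background describes in-person review as labour-intensive and costly to patients, and expects remote administration to save resources. Two of the three advantages listed in the Discussion, avoided travel and protected clinician time, arise when the visit is replaced. Under replacement, a patient seen in person but not reached by telephone would be lost, and the ratio counts that patient correctly. This stands, and it is why the ratio should be kept. It does not remove the gap, because the Discussion attaches better retention to the advantage of reaching patients who cannot return.

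Three stronger readings may tempt a reader, and the documents do not support them:

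- **That the ratio contradicts the promised within-participant comparison.** Each mode's attrition rate is an overall proportion, and the same patients supply both. That sentence promises no analysis of discordant patients.
- **That the planning figures show the ratio will read as no benefit or harm.** This holds only under Reading A. Sample size does not say which half of an incomplete pair is missing, and Reading B points the other way.
- **That the study would conclude against telephone follow-up if the ratio fell below 1.** No null value, test or threshold is stated. This is a descriptive feasibility outcome reported beside contact and return rates.

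Paired reporting may also appear in the separately published analysis plan, which was not available here. The point is therefore confined to the definition that the article states.

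**Conclusion.** The point holds as a limit on what the stated outcome can show. It is not an error in the ratio. The ratio compares telephone with in-person follow-up as alternatives and cannot identify how many in-person non-attenders were recovered. This follows from the algebra and needs no planning assumption: at 85% in-person completion, 1.00 is compatible with no recovery and with 85% recovery.

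The practical size is uncertain. It ranges from 0.94 with half of non-attenders recovered (Reading A) to at least 1.18 (Reading B). These figures illustrate the ambiguity and are not forecasts. The primary accuracy analysis is unaffected. A modest addition to a secondary outcome is proportionate, because it changes what the study can say about retention.

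**What to change.** Keep the ratio and label it as a comparison of telephone with in-person follow-up as a full replacement. Add to the outcome definition, from the paired 2x2 table of telephone questionnaire returned by in-person follow-up completed:

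- (a) the proportion of recruited patients with either assessment, compared with in-person alone;
- (b) the proportion of in-person non-attenders who returned a telephone questionnaire.

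Give confidence intervals that respect the pairing. For (a) expressed as a difference, the estimate is the telephone-only count divided by all recruited patients.

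The cost is a few lines of definition and analysis. The ratio already requires both completion indicators for recruited patients, so no new data are needed.

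State the downsides. Measure (a) as a difference cannot be negative, so it cannot show telephone performing worse. Both (a) and (b) can be inflated if the preceding call deters in-person attendance, a risk the Discussion raises for the existing measure. Measure (b) comes from centres and patients selected as likely to return. Both should therefore be read beside the ratio and the comparison with host-trial attrition that the Discussion mentions. If the published analysis plan already contains these measures, only the article's wording needs to be aligned.

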### Centre selection

Centres for TALON-2 will be chosen based upon (1) the proportion of recruited patients that are likely to return for routine in-person 30-day follow-up and (2) the site’s ability to have an independent non-surgeon researcher perform telephone follow-up for TALON-2 that will not perform in-person, 30-day follow-up. Sites will be selected from across seven low- and middle-income countries (Fig. 1).

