### Study intervention

Telephone-based administration of the WHQ will be compared to the ‘gold standard’ (reference test) of in-person assessment at 30 days after surgery by a trained clinician in accordance with the US Centre for Disease Control criteria (Additional file 2). The WHQ will be delivered integrated into the trial pathway for included patients (Fig. 2). The telephone-based WHQ will be performed at 28–30 days (i.e. in the 72 h prior to in-person follow-up) by a non-surgeon researcher, according to a telephone script. Patients will be asked to provide between one and three telephone contact numbers, either personal or belonging to a family member or community worker. The non-surgeon researcher directing completion of the WHQ should be blinded to the outcome of the in-person wound assessment within the FALCON trial. In the event that the patient is unable to be contacted by telephone at 27–30 postoperative days (before in-person follow-up), the WHQ can be performed after the in-person follow-up appointment, where possible. This should be completed by a non-surgeon researcher that is independent of the assessment for the FALCON primary outcome, to ensure independent measures are taken. The process and pathway for telephone follow-up will be co-designed by patient and public partners to optimise successful and culturally sensitive delivery.

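### The retention-benefit ratio sets no time limit on the telephone WHQ, so calls made after the in-person appointment can count as telephone retention

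*Protocol article*

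**What the plan says.** Retention benefit is the first listed of five secondary outcomes in TALON-2. Under Secondary outcome measures it is the "ratio of the proportion of recruited patients returning a telephone WHQ to the proportion of recruited patients completing in-person" follow-up. The sentence introducing the list explains retention as "maintenance of a patient with trial follow-up to the end of the study, in this case 30 days after surgery". The ratio itself carries no date limit. Neither do the telephone contact rate and the return rate that follow it.

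Under Study intervention, the call is planned for days 28–30, within the 72 hours before the visit. The same paragraph then covers the patient who is "unable to be contacted by telephone at 27–30 postoperative days": in that case "the WHQ can be performed after the in-person follow-up appointment, where possible". No last day is given for this catch-up call, and the two day ranges differ.

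The in-person side is also loosely dated. Eligible patients are those "likely to return for routine in-person follow-up at around 30 days postoperatively are eligible", with no closing day stated.

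The Discussion says that "this study is designed to compare the within-participant attrition rates between in-person and telephone follow-up in-depth". Its limitations paragraph recognises one way in which retention benefit could be overestimated: an early call might discourage attendance. It describes the WHQ as given in the 72 hours before the visit and does not mention calls made afterwards.

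**The concern.** A catch-up call is a sensible way to obtain paired data for the accuracy analysis. It is weaker evidence on retention. A patient who could not be reached before the visit, then attended, and was telephoned afterwards was kept in follow-up by the visit. Under the unqualified definition, that patient enters the numerator exactly as if the telephone had reached them first. The later call is also not independent of the visit, since attendance may have helped the contact, although the documents do not show whether it did.

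The ratio is meant to show what remote follow-up adds to retention, and a reader will take a value above 1 as a benefit of telephone. If catch-up calls are included without being identified, that reading could rest partly on patients whom in-person follow-up had already retained. This is a separate matter from any effect of late calls on sensitivity and specificity.

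**Working it through.** **Reading the passages together.** Four statements matter: a numerator with no time limit; a rule allowing the WHQ after the appointment; a gloss that ties retention to 30 days; and a limitation worded as if every call came before the visit. The first two together admit catch-up calls. The last two suggest that such calls were not in mind when retention was described. Nothing says which governs.

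**Is there a figure to reproduce?** The article states no expected retention benefit, contact rate or catch-up rate. The only anchor is the 15% host-trial loss in Table 1: 714 × 0.85 = 606.9, shown there as 607. Table 1 labels this as patients retained for follow-up. Treating it as in-person completion is an assumption.

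**Formula.** Let q be the share of recruited patients completing in-person follow-up, p the share reached by telephone before the visit, and c the share of those not reached who are recovered by catch-up.

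- Pre-visit calls only: p / q
- Any returned WHQ: [p + c(1 − p)] / q
- Relative increase: 1 + c(1 − p)/p, which does not depend on q and is never below 1

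**Per 5 percentage points of catch-up.** 0.05/0.85 = 0.059. If q were 0.75 this would be 0.067, and if 0.95 it would be 0.053.

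**Range with q = 0.85 (p and c are assumed; the documents give neither):**

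| p | Pre-visit only | c = 0.10 | c = 0.25 | c = 0.50 |
|---|---|---|---|---|
| 0.70 | 0.824 | 0.859 | 0.912 | 1.000 |
| 0.80 | 0.941 | 0.965 | 1.000 | 1.059 |
| 0.85 | 1.000 | 1.018 | 1.044 | 1.088 |
| 0.90 | 1.059 | 1.071 | 1.088 | 1.118 |

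The relative increase runs from 1 + 0.01/0.90 = 1.011 to 1 + 0.15/0.70 = 1.214, that is, about 1% to 21%.

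**How far to trust the crossing of 1.** With p = 0.80 and c = 0.50 the ratio moves from 0.941 to 1.059. Telephone return is then 0.80 + 0.50 × 0.20 = 0.90. With in-person completion of 0.85, at least 0.90 + 0.85 − 1 = 75% of recruited patients would have both assessments. Table 1 plans for 0.85 × 0.85 = 72.25%. Table 1 is a planning allowance and not a forecast, but this cell lies slightly outside it. The table shows what can happen, not what is expected.

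**The case against.** **The counting rule is inferred.** No sentence says that catch-up WHQs enter the ratio, and the 30-day gloss could be read as excluding them. The article also refers to a separate statistical analysis plan, where a closing day might be set. This stands as a limit on the wording, but it does not remove the point. The article states both the ratio and the catch-up rule, and taken as written they combine badly.

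**Extra time for telephone.** A reader might infer that telephone gets a longer window or a second chance that in-person follow-up lacks. The documents do not support this. The visit is only around day 30, no closing day is given, and rebooking of missed visits is neither allowed nor excluded.

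**Net bias in favour of telephone.** A reader might also infer that the ratio as a whole is biased towards telephone. That is not established. Centres are chosen partly on "the proportion of recruited patients that are likely to return for routine in-person 30-day follow-up", and patients are selected on the same ground. Both raise the denominator and push the ratio the other way by an unknown amount. Only the direction of the catch-up component is certain.

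**The pre-visit window serves the accuracy design.** Nothing says that a stand-alone remote pathway would stop calling on the day of a visit. This is fair. Dropping post-visit WHQs from attenders cuts their telephone opportunity short, so a single restricted figure would not be neutral either. It is the reason for showing both versions under one closing day.

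**Importance.** This is a descriptive secondary outcome with no decision threshold, catch-up is a fallback, and comparison with host-trial attrition is already planned. All true. That comparison addresses in-person attendance, however, and does not touch the numerator.

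**Conclusion.** The point holds as a defect of definition. As written, the retention-benefit numerator accepts any returned telephone WHQ, and the study procedures allow some to be obtained after in-person contact. Relative to pre-visit calls alone, this can only raise the ratio, the contact rate and the return rate, or leave them unchanged. It conflicts with the 30-day meaning given to retention in the same section and is missing from the stated overestimation risks.

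The size is unknown. The figure of about 0.06 per 5 percentage points rests on assumed in-person completion of 85%. The 1% to 21% relative range rests on assumed pre-visit contact of 70–90% and assumed recovery of 10–50% of those not reached. Whether the ratio would cross 1 depends on those inputs. The documents do not support a claim about the overall direction of bias.

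**What to change.** 1. State one closing day after surgery that applies to both telephone and in-person follow-up in the retention ratio.
2. Do not count as telephone retention a WHQ first obtained after the patient had already attended in person. A WHQ obtained by the closing day from a patient who never attended does count.
3. Report post-visit WHQs as a separate line, and show the ratio, the contact rate and the return rate with and without them.
4. Reconcile the 28–30 and 27–30 day windows under Study intervention, and mention post-visit calls in the limitations.

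The accuracy analysis need not change, and catch-up calls can continue. The cost is a change of wording and a few extra rows in a table, provided the dates of call and visit are recorded, as the 72-hour rule implies. The article reports TALON-2 recruitment as ongoing, so the definition can still be fixed before analysis. The downside is that the retention benefit may look less favourable.
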